### Baseline and follow-up data

In order to measure the effectiveness of the intervention, the study will employ the following statistical tests: (1) Chi-squared and Mann–Whitney to test homogeneity between the groups at the beginning of the interventions; (2) Student’s t-test or Mann–Whitney to investigate the effects of such interventions, pre and post treatment, depending on the distribution of the data; (3) an analysis of variance, with and without adjustment for mood symptoms scores, IQ and BD duration, for comparison between groups; and (4) the Kaplan–Meyer survival method with log rank test for statistical analysis, to investigate the survival data between groups, which measures in weeks, the time to the first episode as an event. To be considered as an intervention completer, patients assigned to CBR should attend at least eight sessions (66.7%). Intent to treat analyses will be conducted in order to include all available data and missing data will be handled accordingly to the SPIRIT checklist recommendations (Additional file 1).

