**Methods:**

The study consists of a clinical trial comparing a new structured group intervention, called “Cognitive-Behavioral Rehabilitation,” with treatment as usual (TAU) for bipolar patients. The new approach is a combination of cognitive behavioral strategies and cognitive remediation exercises, consisting of 12 weekly group sessions of 90 min each. To be included in the study, patients must be diagnosed with BD type I or II, aged 18–55 years, in full or partial remission, and have an IQ of at least 80. A comprehensive neuropsychological battery, followed by mood, social functioning, and quality of life assessments will occur in three moments: pre and post intervention and 12 months later. The primary outcome of the study is to compare the time, in weeks, that the first full mood episode appears in patients who participated in either group of the study. Secondary outcome will include improvement in cognitive functions.

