### Hypotheses

The study hypothesizes that CBR, compared with TAU, will:Expand the period of time until the first new episode—our primary outcome measure;Improve attention, mental flexibility, working memory, and emotional recognition—our secondary outcome.

In an exploratory analysis, we will also assess whether CBR:Enhances functional, social skills, and quality of life scores;Increases sleep quality and knowledge about the disorder; andReduces impulsivity.

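### The between-arm model for cognitive and functional scores leaves out the outcome's own baseline value, and no version of it is named as the main analysis

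*Protocol article*

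**What the plan says.** The protocol article (Statistical analysis, Baseline and follow-up data) lists four sets of tests. Two of them concern the continuous outcomes after treatment:

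- Item (2): "Student’s t-test or Mann–Whitney to investigate the effects of such interventions, pre and post treatment", with the choice between the two made on the distribution of the data.
- Item (3): "an analysis of variance, with and without adjustment for mood symptoms scores, IQ and BD duration, for comparison between groups".

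The same paragraph adds: "Intent to treat analyses will be conducted in order to include all available data and missing data will be handled accordingly to the SPIRIT checklist".

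The Methods part of the abstract says that the neuropsychological battery and the mood, social functioning and quality-of-life assessments "will occur in three moments: pre and post intervention and 12 months later". A pre-treatment value is therefore planned for these measures.

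The Hypotheses section frames the aims as CBR compared with TAU. The secondary aim is: "Improve attention, mental flexibility, working memory, and emotional recognition—our secondary outcome". Among the exploratory aims is whether CBR "Enhances functional, social skills, and quality of life scores". The primary outcome, time to first episode, is analysed separately by Kaplan–Meier and log-rank.

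**The concern.** The authors chose and listed covariates for the between-group model. That makes this a stated choice and not merely something left to a fuller document. Mood, IQ and illness duration are included. The patient's own pre-treatment score on the outcome, usually the strongest single predictor of the later score, is not. With about 30 patients per arm, the cognitive hypotheses depend on precision, so the omission has a cost.

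Two further features leave room for ambiguity in the eventual report:

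- The model is planned in two versions with no order of precedence, so the one to emphasise could be chosen after the results are seen.
- Item (3) is labelled as the comparison between groups and item (2) is not, so item (2) can be read as a before/after test within each arm. Repeated cognitive tests can improve through practice or time alone. A within-arm change therefore does not show an effect of CBR relative to TAU.

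**Working it through.** **The plan's own figure.** There is none for these outcomes. The sample size section deals only with the proportion episode-free at 12 months, so there is nothing to reproduce on this point.

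**Inputs**
- 60 participants (Sample size section), taken as 30 per arm because that section plans equal groups.
- 80% power and 5% significance, borrowed from the same section. Two-sided testing is assumed, as the article does not say.
- ρ, the correlation between the baseline and follow-up score: not given. Assumed values are 0.3, 0.5, 0.7 and 0.8.
- A true difference of 0.5 SD, used for illustration only: assumed.

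**Formulas.** With equal SDs σ at both times and n per arm, the variance of the estimated arm difference is (2σ²/n) × v, where:
- post-score ANOVA: v = 1
- change-score analysis: v = 2(1 − ρ)
- ANCOVA on the baseline score: v = 1 − ρ²

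The ratio of ANCOVA to change score is (1 − ρ²) / [2(1 − ρ)] = (1 + ρ)/2, which is below 1 for every ρ below 1. The group-by-time test of a two-occasion repeated-measures ANOVA is the same as the change-score test, so the change-score column covers that reading too.

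| ρ | v post | v change | v ANCOVA | ANCOVA / post | ANCOVA / change |
|---|---|---|---|---|---|
| 0.3 | 1.00 | 1.40 | 0.91 | 91% | 65% |
| 0.5 | 1.00 | 1.00 | 0.75 | 75% | 75% |
| 0.7 | 1.00 | 0.60 | 0.51 | 51% | 85% |
| 0.8 | 1.00 | 0.40 | 0.36 | 36% | 90% |

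**What this means at 30 per arm.** The difference detectable with 80% power, in SD units, is (1.96 + 0.84) × √(2/30) × √v = 0.72 × √v.

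| ρ | Detectable difference: post / change / ANCOVA | Power for 0.5 SD: post / change / ANCOVA |
|---|---|---|
| 0.3 | 0.72 / 0.86 / 0.69 | 49% / 37% / 53% |
| 0.5 | 0.72 / 0.72 / 0.63 | 49% / 49% / 61% |
| 0.7 | 0.72 / 0.56 / 0.52 | 49% / 71% / 77% |
| 0.8 | 0.72 / 0.46 / 0.43 | 49% / 86% / 90% |

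With the article's 10% drop-out (30 × 0.9 = 27 per arm) and ρ = 0.7, the powers are 45% / 66% / 73%.

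**Limit of the calculation.** These ratios compare models without other covariates. The planned adjusted version contains IQ, which may already carry part of the information in a baseline cognitive score. Against that version the relevant ratio is 1 minus the squared partial correlation of baseline and follow-up scores given the other covariates. The article gives nothing from which to estimate it.

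**The case against.** Several points on the other side are sound.

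- **Which score is analysed is not stated.** With assessments at three times, change scores or repeated measures are as plausible as post scores. The variances of 75%, 51% and 36% apply only if post scores are analysed. Against change scores, the gain at ρ of 0.7 or 0.8 is only 15% or 10% of the variance. This stands, so both comparators are shown. The direction is the same under either.
- **Incomplete patients.** A reader might infer that t-tests and ANOVA will drop anyone without a follow-up score. The article does not support this. It commits to intention to treat with all available data and to handling missing data, it excludes nobody on this ground, and its definition of a completer is not made an analysis population. The method of handling missing data can properly sit in a fuller document.
- **Ignored pairing.** A reader might also infer that item (2) applies an unpaired test to paired data. Student's t-test can be paired, and Mann–Whitney fits a comparison of the arms at each time or on change. The wording is ambiguous; an error of pairing is not shown.
- **Within-arm significance as efficacy.** Nothing in the article says that efficacy will be judged this way. The hypotheses are comparative and item (3) is explicitly between groups. What stands is that item (2) should be worded so that it cannot be used in that way.
- **Date of the mood score.** It is not fixed, but an analysis plan may settle it. That a score taken after treatment would be used is speculation.

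**Conclusion.** The point holds in a limited form. The listed covariates omit the baseline value of the outcome, which is collected, and neither of the two planned models is given precedence. Adding the baseline score improves precision over a post-score analysis for any non-zero correlation, and over a change-score analysis for any correlation below 1. The gain is large in the first case (variance cut to 75%, 51% or 36% at correlations of 0.5, 0.7 or 0.8) and modest in the second at high correlation (75%, 85% or 90%). It may be smaller again against the version already adjusted for IQ. All correlations are assumed, and the figures rest on equal SDs and equal arms. Item (2) is a matter of unclear wording, not a demonstrated error. The point touches secondary and exploratory outcomes only; the log-rank analysis of the primary outcome is unaffected.

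**What to change.** For each continuous outcome, name one main analysis: an ANCOVA comparing the arms on the follow-up score, with the baseline value of the same outcome, baseline mood scores, IQ and illness duration as covariates. State that its between-arm contrast is the only test of effect. Report the version without the additional covariates (mood, IQ, duration) as a sensitivity analysis. Reword item (2) so that before/after changes within each arm are shown descriptively, without tests of effect.

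A mixed model using both follow-up visits, with the same baseline covariates, is an optional alternative. It would include every patient with any follow-up score, under the assumption that data are missing at random, and so would serve the stated aim of using all available data. It is not needed to meet the point.

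The cost is a change of analysis wording and one degree of freedom per model for the added covariate. The data are already planned for collection. The Trial status section describes the study as underway, so the choice can be recorded before the outcome data are analysed.

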## Statistical analysis

### Sample size

The sample size calculation was based on the proportion of patients that remain episode-free after 12 months following a group intervention. Previous studies utilizing TAU exhibited a decrease of bipolar relapses in 30% of patients after a one-year follow-up [39]. The present study anticipates a 55% success rate in prevention of mood relapses, during the same period, in patients assigned to the CBR. Thus, considering an 80% power to obtain a 5% significance, an estimated sample of 28 individuals per group, 56 in total, should be sufficient to achieve significant results. A previous study conducted by the same research team [14] measured a drop-out rate of 10% in a one-year follow-up. For this latter reason, the study will consist of 60 participants.

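### The between-group ANOVA names its covariates but leaves out the baseline value of the score being analysed, so the secondary and exploratory comparisons give up precision that is already paid for

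*Protocol article*

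**What the plan says.** The section on baseline and follow-up data in the protocol article lists four procedures. Item (1) uses chi-squared and Mann–Whitney tests "to test homogeneity between the groups at the beginning of the interventions". Item (2) uses a t-test or Mann–Whitney test "to investigate the effects of such interventions, pre and post treatment, depending on the distribution of the data". Item (3) is "an analysis of variance, with and without adjustment for mood symptoms scores, IQ and BD duration, for comparison between groups". Item (4) is the Kaplan–Meier and log-rank analysis of the primary outcome, "which measures in weeks, the time to the first episode as an event".

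The abstract states that "assessments will occur in three moments: pre and post intervention and 12 months later", so a pre-treatment value of each analysed score is planned. The scores concerned serve the secondary hypothesis ("Improve attention, mental flexibility, working memory, and emotional recognition") and the exploratory aims, among them "Enhances functional, social skills, and quality of life scores".

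Nothing in the article puts the baseline value of a score into the model for that score at follow-up.

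**The concern.** For a cognitive test or a functioning scale, the patient's own earlier score is usually the best available predictor of the later one. Item (3) does plan adjustment and names three covariates, so leaving out the baseline score is a stated choice and not a detail deferred to a document we have not seen. The use of baseline in item (1), a homogeneity test, does not make the outcome comparison any more precise.

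With about 30 patients per arm, two things are at stake. The standard error is larger than it need be. And if the arms happen to differ at baseline on a given test, part of that difference passes into the estimated effect. The sample was sized on episode-free proportions only, so nothing else in the design protects precision for the cognitive scores.

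**Working it through.** **Plan's own figure.** There is none for these scores. The sample-size section gives "an estimated sample of 28 individuals per group, 56 in total" for the primary outcome, which does not bear on this point.

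**Inputs from the article.** 60 participants, taken as 30 per arm; 10% drop-out, hence 30 × 0.9 = 27 per arm; 5% significance, taken as two-sided; 80% power.

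**Assumptions.** The correlation r between baseline and follow-up is not in the article; the range is 0.3 to 0.8. The SD is taken as equal at both times and set to 1.

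**Residual variance relative to an unadjusted follow-up comparison**
- Follow-up score only: 1
- Change score, or a pre/post group-by-time test: 2(1 − r)
- Follow-up score adjusted for baseline: 1 − r²

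The small cost of estimating the baseline slope is ignored.

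**1. Against an unadjusted follow-up comparison.** The two-sample t-test with 27 per arm detects 0.777 SD. Multiplying by √(1 − r²) gives the baseline-adjusted value; the change-score value uses √(2(1 − r)).

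| r | 1 − r² | Adjusted, detectable SD | 2(1 − r) | Change score, detectable SD |
|---|---|---|---|---|
| 0.3 | 0.91 | 0.74 | 1.40 | 0.92 |
| 0.5 | 0.75 | 0.67 | 1.00 | 0.78 |
| 0.7 | 0.51 | 0.55 | 0.60 | 0.60 |
| 0.8 | 0.36 | 0.47 | 0.40 | 0.49 |

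**2. Against a change-score or pre/post group-by-time analysis.** The variance ratio is (1 − r²) / [2(1 − r)] = (1 + r)/2. That is 0.75 at r = 0.5, 0.85 at 0.7 and 0.90 at 0.8.

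**3. Against the planned adjusted model.** Suppose the listed covariates explain a share R² of outcome variance, and correlate equally with the baseline and follow-up scores (assumption). The partial correlation of baseline with follow-up is then (r − R²)/(1 − R²), and adding baseline multiplies the residual variance by 1 minus its square.
- R² = 0.10, r = 0.5: partial 0.444, factor 0.80, a cut of 20%
- R² = 0.30, r = 0.5: partial 0.286, factor 0.92, a cut of 8%
- R² = 0.10, r = 0.7: partial 0.667, factor 0.56, a cut of 44%
- R² = 0.30, r = 0.7: partial 0.571, factor 0.67, a cut of 33%

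**4. Chance imbalance.** With 30 per arm the baseline difference between arms has SD √(2/30) = 0.258. The probability that it exceeds 0.3 SD in either direction, on a given test, is 24.5%; the 95% range is ±0.51 SD. An unadjusted follow-up comparison carries r times the gap: for a gap of 0.51 SD, about 0.25 SD at r = 0.5 and 0.35 SD at r = 0.7. A change score carries −(1 − r) times the gap, so about 0.25 SD and 0.15 SD in the opposite direction.

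**The case against.** The strongest reply is that the model is not identified. The article names neither the dependent variable nor the factors of the ANOVA. With three assessment times, a repeated-measures analysis is a natural reading, and baseline then enters as a level of time without being listed as a covariate. This stands as a limit on size: at r = 0.7 or 0.8 the change-score reading detects 0.60 or 0.49 SD, against 0.55 or 0.47 with baseline adjustment. It does not remove the point, because adjustment for baseline has the smaller residual variance on that reading too.

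A reader might go further than the article allows in four ways.
- That item (3) is the only between-arm comparison of these scores. Mann–Whitney is an independent-samples test, so item (2) may also compare the arms, possibly on change.
- That the plan removes no between-patient variance. The adjusted version of item (3) removes whatever mood, IQ and illness duration explain, and IQ may partly stand in for baseline cognition.
- That the whole fall from 0.78 to 0.47 SD is what the plan loses. That figure compares with a model without covariates, at the top of the assumed range of r. At r = 0.3 the variance saved is only 9%.
- That the comparisons are biased. Randomisation makes them unbiased on average; what remains is precision and imbalance in the one trial that is run.

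It is also fair to say that these outcomes are secondary or exploratory, in a study that describes itself as proof of concept.

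**Conclusion.** The point holds as a free improvement. The covariate list omits the one variable likely to help most, and that variable is already collected. Its inclusion lowers residual variance on a follow-up, change-score or pre/post group-by-time reading, and beyond the listed covariates as well. The gain runs from small (8% of residual variance when the listed covariates explain 30% and r = 0.5; 9% against no covariates at r = 0.3) to large (44% when they explain 10% and r = 0.7). No single figure can be given, because neither r, nor the share explained by the listed covariates, nor the form of the ANOVA is in the article. Neither the primary analysis nor the validity of the randomised comparison is in question.

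**What to change.** Restate item (3) as an analysis of covariance. The outcome is the score at each post-baseline time, post-intervention and 12 months, analysed separately or in one repeated-measures model. The terms are arm, the baseline value of the same score, and baseline mood scores, IQ and BD duration. Say explicitly that the mood scores are the baseline ones, since mood is assessed at all three times. Report the adjusted mean difference with its 95% confidence interval for each score.

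The cost is a sentence or two in the analysis section, settled before data are analysed by arm, and one degree of freedom per model. It needs no new data, visits or patients.

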## Background

Bipolar disorder (BD) is a severe medical condition often associated with functional impairments even when affected individuals are euthymic [1]. Many studies report cognitive deficits in this population, most often in executive functions [2], attention [3], and verbal memory [4], which is coherent with recent meta-analyses on this topic [5, 6]. Recent studies have also established an association between cognitive deficits and functional impairments [7]. This evidence leads some authors to suggest that bipolar patients should benefit from cognitive rehabilitation strategies similar to those conducted in patients with schizophrenia [8].

Structured psychotherapies for BD associated with standard pharmacotherapy are associated with longer periods of remission, reduction in manic and depressive symptomatology, and faster recovery from episodes when compared to pharmacological treatment alone [9]. The majority of current studies suggest psychotherapy as an add-on to pharmacological treatment, even during euthymic periods [10].

Some studies have reported negative results regarding the effects of psychotherapies in preventing new mood episodes in BD [11]. A multicenter study including 253 patients with BD, in a heterogeneous sample with patients in diverse mood states, identified that Cognitive Behavior Therapy (CBT) prevented new mood episodes only in patients with less than 12 previous episodes [12]. Similar negative results in recovering and preventing mood episodes were found in group psychotherapy settings [13, 14]. The effectiveness of structured approaches most likely depends on the number of previous mood episodes [15]. Most negative studies included more severe presentations of BD, often including patients with more than two co-morbidities or many previous mood episodes; these observations have guided some researchers to delineate the importance of a staging model in BD [16].

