### Participants

In order to be included, patients must be aged 18–55 years, literate, present an IQ score higher than 80, have been diagnosed with bipolar I or II based on Structured Interview for DMS IV (SCID) [27], and be in full or partial remission according to the DSM IV [28]. Exclusion criteria are: presence of substance or alcohol abuse in the last six months; current suicide risk; organic mental disorders; or scores higher than 12 in the Montgomery-Åsberg Depression Rating Scale (MADRS) or the Young Mania Rating Scale (YMRS) at the beginning of the intervention [28].

Recruiting will take place at an outpatient service provided by the Bipolar Disorder Research Program (PROMAN) at the University of São Paulo Medical School, Brazil. Patients will receive invitations individually and sign an informed consent. This research was approved by an internal ethical committee and registered in ClinicalTrials.gov: NCT02766361.

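### The primary survival comparison is planned unadjusted, while covariate adjustment is attached only to the analysis of variance; a prespecified adjusted Cox model would be a cheap gain in precision

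*Protocol article*

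**What the plan says.** The Abstract (Methods) defines the endpoint: "The primary outcome of the study is to compare the time, in weeks, that the first full mood episode appears". The Hypotheses section also makes it the primary measure.

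The section Baseline and follow-up data lists four analyses in one sentence. Two of them matter here:

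- The third is "an analysis of variance, with and without adjustment for mood symptoms scores, IQ and BD duration, for comparison between groups". It does not say to which outcomes this applies.
- The fourth, for time to first episode, is "the Kaplan–Meyer survival method with log rank test for statistical analysis, to investigate the survival data between groups". No covariate, stratum or hazard ratio is named.

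The first item in the list plans tests of homogeneity between the arms at the start. The protocol does not say what follows for the primary comparison if the arms differ.

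On the patients, the Participants section requires that they "be in full or partial remission according to the DSM IV" and excludes only MADRS or YMRS scores above 12. The Background says: "The effectiveness of structured approaches most likely depends on the number of previous mood episodes".

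**The concern.** The authors judged three patient characteristics worth adjusting for, but attached the adjustment to a method that cannot use censored follow-up time. The comparison that decides the trial has none. Entry admits both full and partial remission and a range of residual symptoms, so relapse risk may well vary between patients. With 30 per arm, noticeable chance imbalance in any one factor is not rare.

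Two things are at stake. The first is precision: if a baseline factor predicts relapse, leaving it out of a time-to-event analysis lowers power, and this trial has little to spare. The second is prespecification: homogeneity tests with no stated consequence leave room to decide on adjustment after the imbalance, or the result, has been seen.

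**Working it through.** **Inputs from the protocol (Sample size section).** Episode-free at 12 months: 0.30 under treatment as usual ("Previous studies utilizing TAU exhibited a decrease of bipolar relapses in 30% of patients after a one-year follow-up", ambiguous wording, read here as the proportion episode-free) and 0.55 under the intervention ("The present study anticipates a 55% success rate in prevention of mood relapses, during the same period, in patients assigned to the CBR"). Significance 5% (two-sided assumed, as sidedness is not stated), power 80%, 28 per group, 60 patients in all.

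**The plan's own figure.** A two-sided two-proportion test needs

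n = [1.96·√(2·0.425·0.575) + 0.842·√(0.30·0.70 + 0.55·0.45)]² / 0.25² = (1.370 + 0.569)² / 0.0625 ≈ 60.2, so 61 per arm.

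The stated 28 is not reproduced; a one-sided test still needs 48. That is a separate matter. It is needed here only to fix the power at which the primary test operates.

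**Power of the planned log-rank test, 30 per arm, proportional hazards.**

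- Hazard ratio: ln 0.55 / ln 0.30 = 0.497, so the log hazard ratio is −0.700.
- Expected events: 60 × (0.70 + 0.45)/2 = 34.5.
- Standard error of the log hazard ratio: 2/√34.5 = 0.34.
- Power: Φ(0.700/0.3405 − 1.96) = Φ(0.096) ≈ 54%.

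The two-proportion test at 30 per arm has about 50%.

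**How large chance imbalance can be.** For a factor present in half the patients, under simple randomisation with 30 per arm, the probability that the arms differ by at least 6 of 30 (20 points) is 0.155. If that factor doubled the hazard (assumed), a 20-point imbalance would move the unadjusted hazard ratio by a factor of about exp(0.2 × ln 2) = 1.15. On the log scale that is 0.14, or 0.14/0.34 ≈ 0.4 standard errors, in either direction.

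**What adjustment gains.** The documents give no covariate effect, so a range is assumed: one standard normal baseline covariate, 30 per arm, 12-month episode-free proportions held at 30% and 55% overall, no dropout, Cox Wald test at two-sided 5%, 2,000 simulated trials per row (Monte Carlo standard error about 1 point).

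| Assumed log hazard ratio per SD | Unadjusted power | Adjusted power | Gain (points) |
|---|---|---|---|
| 0 | 50% | 51% | about 1 |
| 0.4 | 52% | 56% | about 5 |
| 0.8 | 55% | 71% | about 17 |

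Gains are taken from unrounded powers.

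**Sensitivity to calibration.** If 30% and 55% are instead taken as the proportions for a patient with an average covariate value, unadjusted versus adjusted power is 47% vs 52%, 43% vs 52% and 40% vs 51% for hazard ratios per SD of 1.5, 1.8 and 2.0. The level of unadjusted power depends on this choice, but adjustment gains under both. With no true treatment effect, the rejection rate stayed at about 4% to 6% with and without adjustment.

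**The case against.** The strongest reply is that an unadjusted log-rank test is a standard and valid primary test in a randomised trial, that its error rate already allows for chance imbalance, and that a condensed article may leave a hazard ratio or a supportive Cox model to a fuller plan. The first two parts stand, so the point is about efficiency and prespecification. On the third, a missing hazard ratio and interval would not be a finding alone. What remains is that the article fixes an unadjusted primary comparison while placing the adjustment elsewhere.

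A reader might infer several stronger things that the text does not support:

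- *That the protocol names strong prognostic factors and ignores them.* It calls no variable prognostic for relapse. The Background passage on previous episodes, and the cited trial in which therapy "prevented new mood episodes only in patients with less than 12 previous episodes", describe a factor that changes the treatment effect. That calls for an interaction or strata; a main-effect covariate would not address it. The count is also not in the adjustment list, and the article does not say it is recorded.
- *That only secondary analyses are adjusted.* The analysis of variance is not assigned to any outcome.
- *That the primary analysis yields only a p-value.* Kaplan–Meier gives the episode-free proportion in each arm over time, including at 12 months, and medians where reached.
- *That imbalance biases the result.* A 20-point imbalance in a factor that doubles the hazard is worth about 0.4 standard errors, in either direction.

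The objection that 40 patients were already included also has some force: this would change the primary analysis of a running trial, and is clean only if made before any comparison by arm.

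**Conclusion.** The point holds as a cheap improvement and does not show an error in the plan. The primary test is valid but leaves out covariates that the protocol itself thought worth using, and chance imbalance is left without a prespecified response. The size is about 0 to 17 points of power, resting entirely on an assumed log hazard ratio of 0 to 0.8 per SD, two-sided testing, proportional hazards and no dropout. A covariate with no effect cost nothing measurable in the simulations. Power stayed below 80% throughout the range examined, so adjustment is no substitute for correcting the sample size.

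**What to change.** Before any comparison by arm, prespecify as the primary analysis a Cox model for weeks to first full mood episode with arm as the effect of interest, reporting the hazard ratio and 95% confidence interval. Adjust for one or two covariates the protocol already names: baseline mood score (for example MADRS) and illness duration. State that the mood score is the pre-intervention value, since the article does not give the time point. Keep the Kaplan–Meier curves and the unadjusted log-rank test as supporting analyses, and say that the homogeneity tests will not alter the covariate set.

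Use the number of previous episodes only if it is recorded at entry, and examine it as a possible effect modifier.

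The cost is a wording change, documented and dated as an amendment to a running trial, with no new data for mood score and illness duration. Statistically it costs one or two degrees of freedom against about 35 events and adds a proportional-hazards assumption to be checked. The resulting hazard ratio is conditional on the covariates, so it is not directly comparable with an unadjusted one.
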